### Sample size

Published data for a sample of 32 high-risk preschool children (had PTSD 1 month post-burn) who received TAU indicate that their PTSS decreased by an average of three symptoms (from 7 [SD = 2.1] to 4 [SD = 3.3]) over 6 months [3]. We assume that, over the course of 6 months, the number of symptoms in participants in the CARE group will have a mean reduction of five (SD = 3) and the number of symptoms in participants in the TAU groups will have a mean reduction of three (SD = 3). These data are based on the level reported in the recovered high-risk children (i.e., those who no longer met PTSD diagnostic criteria at 6 months) [3]. Consequently, we anticipate the mean difference in the number of symptoms between the CARE and TAU groups at 6 months will be two. We assume the SD will be 3 symptoms and an α-level of 0.05. Using a two-sided test, a total sample size of 56 children (28 in each treatment group) is required to complete the study with a power of 80 %. This is equivalent to an effect size of 0.75. We anticipate that approximately 25 % of participants will not complete the 6-month interviews; therefore, we will randomise 76 individual children to get complete primary outcome data for 56 participants.

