### Statistical analysis plan

Prior to investigating treatment outcome, the intervention and control groups will be compared for pre-treatment equivalence by using demographic and baseline measures (e.g., sex, age, injury severity, child PTSS, parent PTSS). If significant differences are found (*p* < 0.001), this will be taken into account by including these variables as covariates in outcome analyses. The association between completers and non-completers and baseline characteristics will be investigated using Fisher’s exact test and Student’s *t* tests. The outcome data will be analysed and reported in terms of statistical significance of differences between groups in change over time, adjusting for the value of the outcome at baseline. To test the association between treatment group and outcome, we will do a linear regression, with the main outcome being change over 6 months and the independent variables being treatment group (CARE or TAU), and the baseline score on the outcome under investigation will be included as a co-variable. When appropriate, repeated-measures analyses will be used to compare the two groups with respect to improvement over time. Generalised estimating equations and generalised linear mixed models will be employed. For sensitivity analysis, if any systematic differences are found according to assessment completion, we will re-run analyses using 3- and 6-month outcome data imputed using multiple imputation techniques. Analyses will be conducted on an intention-to-treat basis, with individuals analysed on the basis of the groups to which they were randomised, regardless of the treatment they received. We define statistical significance as *p* < 0.05.

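### The main 6-month regression leaves out about a quarter of randomised children, and the only stated remedy, multiple imputation, depends on baseline completer tests that cannot show whether it is needed

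*Protocol article*

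**What the plan says.** All references are to the protocol article.

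- **Main test** (Statistical analysis plan): "we will do a linear regression, with the main outcome being change over 6 months", with treatment group and the baseline score as independent variables.
- **Other models** (same section): "Generalised estimating equations and generalised linear mixed models will be employed". The preceding sentence limits repeated-measures analyses to where they are appropriate. Neither sentence makes them the main analysis.
- **Completer check** (same section): "The association between completers and non-completers and baseline characteristics will be investigated using" Fisher's exact test and t tests. No separate threshold is given for this check.
- **Imputation** (same section), as a sensitivity analysis: "if any systematic differences are found according to assessment completion, we will re-run analyses" with 3- and 6-month outcomes multiply imputed.
- **Analysis set** (same section): "Analyses will be conducted on an intention-to-treat basis, with individuals analysed on the basis of the groups to which they were randomised", whatever treatment they received.
- **Expected loss** (Sample size): "We anticipate that approximately 25 % of participants will not complete the 6-month interviews". The plan is to randomise 76 so that 56 have complete primary outcome data.

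**The concern.** A child without a 6-month DIPA interview has no value for 6-month change and so drops out of the regression. That is safe if dropout depends only on arm and baseline score, because both are in the model. It is not safe if dropout depends on how the child was doing at 3 months and that dependence is not the same in the two arms. An example would be TAU families who are still distressed leaving while CARE families leave at random.

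The 3-month DIPA is scheduled for every child (Table 2) and carries information on exactly this, but the main regression does not use it. The analysis that would use it, imputation, is run only after a positive result from tests that look at baseline characteristics. Even when triggered, imputation stays a sensitivity analysis, so the main estimate does not change.

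**Working it through.** **1. Planned missingness.** Inputs from Sample size: 56 completers needed, 25% loss, 76 randomised. 56 / (1 − 0.25) = 74.7, so 75. The stated 76 is the next multiple of the block size of four, so the figure reproduces. Non-completers: 76 − 56 = 20, and 20 / 76 = 26.3%.

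**2. Power of one completer t test.** 56 v 20, two-sided 0.05 (assumed, as the article's general significance level). The noncentrality is d × √(56 × 20 / 76) = 3.84d, on 74 degrees of freedom.

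- d = 0.3: 21%
- d = 0.5: 47%
- d = 0.8: 86%
- 80% power needs d of about 0.74

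Fisher's exact test has 28% power for 50% v 70% and 43% for 50% v 75%.

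**3. Chance firing.** The condition is met by any difference over an unstated number of variables. With k independent tests at 0.05 and no real difference, the chance of at least one positive is 1 − 0.95^k: 23% for k = 5 and 40% for k = 10.

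**4. Size of a possible bias.** The article gives no dropout mechanism and no correlations, so this step is an illustration. Assumptions:

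- 38 children per arm; SDs 2.1 (baseline), 3.2 (3 months) and 3.3 (6 months). The first and last are the SDs cited under Sample size; 3.2 is assumed.
- Correlations 0.45 (baseline with 3 months), 0.45 (baseline with 6 months) and 0.7 (3 with 6 months).
- All children have a 3-month score, and 25% per arm lack the 6-month score.
- Dropout log-odds are linear in the child's 3-month deviation from the arm mean, with the slopes per SD shown below.
- 4000 runs per row; true 6-month difference 2.

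The likelihood estimate regresses the 6-month score on arm, baseline and 3-month score in completers, and the 3-month score on arm and baseline in all children. It then combines the two. The last column is how often a t test of baseline PTSS, completers v non-completers, gives p < 0.05.

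| Slope TAU / CARE | Completers-only regression | Likelihood, using 3-month score | Baseline PTSS test positive |
|---|---|---|---|
| 0 / 0 (random) | 2.0 | 2.0 | about 5% |
| 1 / 1 (same) | 2.0 | 2.0 | about 30% |
| 0.5 / 0 | 1.8 | 2.0 | about 7% |
| 1 / 0 | 1.6 to 1.7 | 2.0 | about 11% |
| 0.5 / −0.5 | 1.6 | 2.0 | about 5% |
| 1 / −1 | 1.3 | 2.0 | about 5% |

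With no true effect, the 1 / −1 row gives an estimate of about −0.7 and 15% false rejections. The 1 / 0 row gives about −0.4 and 7 to 8%.

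The last column shows the problem with the trigger. In this illustration the baseline PTSS test is positive most often where the regression is unbiased (1 / 1), and at its chance rate where the bias is largest (1 / −1).

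**The case against.** The strongest reply is that the article already plans mixed models. A likelihood mixed model keeps children who have a 3-month but no 6-month score, and the primary hypothesis covers both time points, so repeated measures fit the stated aim. This stands in part: the remedy is largely a promotion of something already planned. It does not remove the point, because the article names the regression as the test of treatment effect and leaves the other models to be used where appropriate. Imputation detail can be left to a fuller plan, but the trigger is a rule that the article itself states.

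Several stronger readings are tempting and are not supported:

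- **That the intention-to-treat statement is contradicted.** The article defines it only as analysis by randomised group regardless of treatment received, and it openly plans for 56 complete of 76.
- **That unequal dropout rates between arms bias the result by themselves.** They do not, since arm is in the model. Bias needs dependence on later symptoms that differs by arm.
- **That the result will be biased.** No figure in the article supports any particular dropout pattern, and opposite directions in the two arms is an adverse assumption.
- **That imputation is triggered only 21% or 47% of the time.** Those are single-test figures. Several tests together fire more often, partly by chance.
- **That a negative completer test is declared proof that missing data can be ignored.** The article does not say so; it only makes imputation depend on the test.

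**Conclusion.** The point holds as a fault in a stated rule. The main analysis rests on about 74% of randomised children, and whether the imputed analysis is run depends on tests that are individually insensitive, collectively prone to chance and aimed at baseline only.

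The missing fraction (26%) follows from the article's own figures. The test powers follow from its numbers and an assumed 0.05 threshold. The bias is conditional: none under random dropout or the same dependence in both arms, about 0.2 to 0.4 symptoms out of 2 if dependence is in one arm only, and about 0.4 to 0.7 if it runs in opposite directions, for slopes of 0.5 to 1 per SD. These sizes rest on assumed correlations and mechanisms, and on every child having a 3-month score. The article gives no 3-month dropout figure, so the gain from using that score may be smaller. The change is worth making because it is cheap, not because bias has been shown.

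**What to change.** 1. Name the already planned mixed model as the primary analysis: 3- and 6-month DIPA scores, with arm, time, arm-by-time and baseline score. Include all children with any follow-up score, analysed as randomised, and take the 6-month arm contrast as the primary estimate.
2. Delete the trigger. Run multiple imputation in every case, with the 3-month score in the imputation model. Keep the completer comparison as description only.
3. Both analyses assume missing at random, so add a simple delta-adjusted sensitivity analysis in which imputed 6-month scores are shifted by stated amounts, including shifts that differ by arm.

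The cost is revised wording and a little more programming; no new data are needed. The drawback is that the primary result then relies on the missing-at-random assumption, which step 3 is there to examine.

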### Dissemination policy

Outcomes will be published in peer-reviewed journals and will also be presented at relevant national and international conferences. Findings will also be disseminated broadly to participants, health care professionals and the public. If the CARE intervention proves to be effective, implementation in other hospitals is planned.

## Discussion

Currently, research suggests that early preventive interventions may be beneficial for reducing distress associated with childhood injury. However, further empirical evidence is needed to determine optimal timing, length and content needed for interventions to be effective in preventing the development of persistent PTSD and co-morbid conditions. In particular, despite infants, toddlers and pre-schoolers being a particularly at-risk population, to date, the mental health needs of this group are under-recognised and there is very little evidence available to inform research and clinical practice with this population. Health service providers need to become better skilled at detection and treatment of post-traumatic stress reactions in young children.

This international collaboration therefore is an excellent opportunity to test the potential benefit of screening and providing early intervention to young injured children in two different countries and settings. Screening for risk is important because the majority of children, particularly those treated by outpatient hospital services, are not routinely identified and provided with psychological support options. Routine screening has the potential to identify families that are unlikely to engage in mental health treatment as well as improve the efficiency and cost-effectiveness of hospital services. Provision of psychoeducation and coping skills to promote resilience and recovery has the potential to prevent the development of chronic PTSD and co-morbid disorders (that could be later misdiagnosed and mistreated, such as medication for attention-deficit/hyperactivity disorder) and improve treatment adherence and physical recovery (thus improving clinical efficiency with reductions in treatment and rehabilitation duration). Intervening during early childhood, before problems become entrenched and negatively impact critical early development, has the potential to diminish the burden of disease and dysfunction across the lifespan. Given the high incidence of paediatric injury worldwide, a successful early intervention programme for this at-risk population could have significant implications for the social and economic costs associated with medical trauma and beyond.

It is expected that outcomes from this research will make significant original contributions to the clinical treatment and recovery of very young, unintentionally injured children, adding to the resource and scientific evidence base. The parallel research studies evaluating this intervention in Australia and Switzerland highlight the international significance of this problem and will strengthen the generalisability of our findings. Altogether, the findings will help increase the impact and awareness of this important area internationally.

## Trial status

The Australian study commenced recruitment on 3 June 2014 and the Swiss study did so on 1 April 2014. The recruitment for both trials is expected to be completed by the end of 2016 and final assessments by mid-2017.

## Abbreviations

CARE, Coping with Accident Reactions; CBCL, Child Behavior Checklist; CONSORT, Consolidated Standards of Reporting Trials; DIPA, Diagnostic Infant and Preschool Assessment; DSM-5, *Diagnostic and Statistical Manual of Mental Disorders, Fifth Edition*; LCCH, Lady Cilento Children’s Hospital; PDS, Posttraumatic Diagnostic Scale; PEDS-ES, Pediatric Emotional Distress Scale-Early Screener; PMTS, Pediatric Medical Traumatic Stress; PPPHM, Pediatric Psychosocial Preventative Health Model; PTE, potentially traumatic event; PTSD, post-traumatic stress disorder; PTSS, post-traumatic stress symptoms; RCT, randomised controlled trial; RTA, road traffic accident; SPIRIT 2013, Standard Protocol Items: Recommendations for Interventional Trials; TAU, treatment as usual; TF-CBT, trauma-focused cognitive behavioural therapy
